**IVR daily monitoring questions**

The IVR protocol consists of 30 primary questions with 25 additional secondary questions that may be asked, depending on the responses to the primary questions. The IVR program automatically blocks invalid responses and alerts the respondent that they need to make a valid entry. Research on mechanisms of change in treatment of PTSD and alcohol use has typically relied on retrospective reconstruction of hypothesized precipitants of alcohol cravings and drinking behaviors. Because of the use of simple pre-post treatment designs or weekly symptom measures these studies make it harder to examine the interrelationships between PTSD and alcohol use during psychotherapy or to better understand both positive treatment outcomes and non-responders. However, researchers examining negative affect and alcohol use and other addictive behaviors like smoking in non-trauma samples have increasingly begun to utilize daily monitoring of symptoms to examine predictors of substance use and lapses.

**Baseline Monitoring Phase**

Participants begin calling the IVR system the day after their baseline appointment and the following week is considered to be the baseline-monitoring period. If the participant is randomized to CPT or RP, the baseline-monitoring period continues until the first therapy appointment occurs. Participants must call the IVR system for at least 4 of 7 days following baseline or they will be determined ineligible for the study. If participants fail to make the calls, staff can collect the data by phone within 3 business days of missed IVR calls. If the baseline-monitoring period extends for longer than a week due to conflicts in scheduling the first therapy appointment, participants must continue to call (or make up the missed calls with staff) at least 60% of the days. If necessary, the baseline-monitoring period may be extended for a total of 4 weeks.

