**Randomization**

Participants who meet all inclusion/exclusion criteria are randomly assigned to CPT, RP or AO by the UW research coordinator using a randomization table created for the study. An adaptive randomization protocol is used to insure that the two groups are balanced with respect to baseline severity of AUD, severity of PTSD symptoms and gender. Baseline severity of AUD is dichotomized based on presence of Alcohol Dependence with physiological dependence. Baseline severity of PTSD is dichotomized based on Clinician Administered PTSD scale scores > 59, which indicates severe PTSD.

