**Safety and Comfort call**

All participants are informed that a clinical staff member will call them the next business day after the baseline appointment. For those who are ineligible at the baseline assessment, the call is made by the clinical assessor and the purpose of the call is to assess for symptom exacerbation from the baseline visit and to provide support and normalization or to intervene clinically as needed. For those who are eligible, the call is made by the participant’s therapist and in addition to assessing for safety, the purpose is to ask about how the first IVR call went and to let him or her know whether s/he was randomized to the AO condition or to start one of the 2 therapies at the end of a week of baseline monitoring. The therapist making the call does not yet know which therapy the participant will receive but they schedule the first appointment or the first AO check-in call for the following week.

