   4. Individuals whose Blood Alcohol Concentration (BAC) was over 0.0 were asked to either wait until their BAC drops to 0.0 or to reschedule the appointment.
   5. Individuals went through a 2.5- to 3.5-hour assessment to confirm eligibility and to complete questionnaires.
   6. Individuals who were found to be eligible were shown how to use the Interactive Voice Response (IVR) system and were introduced to the site study clinician who called them the next business day to check on symptom exacerbations, provide support and normalization or intervene clinically as needed, and provide IVR support:
      1. The AO participants called the IVR system daily for seven weeks before they were re-randomized.
      2. The CPT and RP participants called the IVR system for one to four weeks before they started their individual therapy (baseline monitoring period). When the baseline-monitoring period was extended due to conflicts in scheduling the first therapy appointment, the participants were expected to continue calling the IVR system at least 60% of the days.
   7. During the first week of IVR calls (baseline calls), the study staff called the participants to let them know if they were randomized into the CPT, RP, or AO group.
5. Treatment Sessions:
   1. Participants randomized to either the CPT or RP group met with their study clinician for 60 minutes twice per week for 6 weeks (rescheduled appointments could be extended into week 20.
   2. The therapist informed the participants of their study condition (CPT or RP) at their first therapy session.
   3. At the beginning of each treatment session, the participants:
      1. took a breathalyzer test. If their BAC was over 0.02, they were asked to wait until their BAC dropped below 0.02 or to reschedule.
      2. complete short questionnaires to track homework compliance.
   4. Participants were also asked to complete short weekly questionnaires to monitor their PTSD symptoms and substance abuse prior to the first therapy session of the week.
6. Assessments:
   1. Participants completed a post-treatment assessment within one month of completing their treatment.
   2. Participants repeated the assessment battery 3- and 12- months post-treatment.
   3. Participants were given a choice to complete the post-treatment, 3-month, and 12-month assessments in-person or by phone. The study assessor collected clinical measures already approved for use in the assessments in a short telephone interview.

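### The 4-of-7-day IVR call rule removes participants after they have been randomised and told whether they are in assessment only or therapy, which can bias the comparison with assessment only

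*Protocol*

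**What the plan says.** All of these statements are in the protocol.

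- **Randomization:** "Participants who meet all inclusion/exclusion criteria are randomly assigned to CPT, RP or AO by the UW research coordinator". The IVR call rule is in neither list of inclusion and exclusion criteria.
- **Safety and Comfort call:** "All participants are informed that a clinical staff member will call them the next business day after the baseline appointment". For eligible participants one purpose of the call is "to let him or her know whether s/he was randomized to the AO condition or to start one of the 2 therapies". CPT versus RP stays concealed: "The therapist making the call does not yet know which therapy the participant will receive".
- **Baseline Monitoring Phase:** IVR calls start the day after the baseline appointment, and the week that follows is the baseline-monitoring period. Then: "Participants must call the IVR system for at least 4 of 7 days following baseline or they will be determined ineligible for the study". Staff may collect missed data by phone within 3 business days. If the first therapy appointment is late, "participants must continue to call (or make up the missed calls with staff) at least 60% of the days".
- **Therapy Visits**, and STUDY DESIGN item 5.2 in the overview of final modifications: CPT or RP is disclosed at the first session.
- **STUDY DESIGN item 4.7:** in the first week of calls, "the study staff called the participants to let them know if they were randomized into the CPT, RP, or AO group".
- **Premature discontinuation:** continued follow-up (retrieved dropouts) is described for participants taken off treatment because their clinical status deteriorates.
- **TOTAL ENROLLMENT:** 101 randomised (CPT 41, RP 38, AO 22). The text does not say whether this is before or after removals under the IVR rule.

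**The concern.** An eligibility test does no harm to a randomised comparison if it is settled before allocation. Here it is settled afterwards, on behaviour that the allocation can influence. Someone seeking therapy who learns that seven weeks of phone monitoring come first may call less than someone about to start therapy; the opposite is also conceivable. Those who stop calling may also differ in drinking or PTSD severity. If removal rates differ by arm, the participants who remain are no longer comparable.

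AO is the only untreated comparator. The first hypothesis is that both therapies do better than AO over the six-week treatment period and at post-treatment, so that is the contrast at stake. AO is also the smallest arm: one removal from 22 is 1/22 = 4.5% of it.

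The same sequence also means that the baseline IVR week is not a clean pre-randomisation measure, since most of it is recorded by people who know whether therapy is about to start.

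**Working it through.** The plan gives no figure to reproduce here. The check has two parts: the order of events, and an illustration of size.

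**1. Order of events**

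- IVR day 1 is the day after the baseline appointment. The disclosure call is due on the next business day.
- For an appointment from Monday to Thursday in an ordinary week, disclosure falls on IVR day 1, and 7 − 1 = 6 of the 7 days come later.
- For a Friday appointment, disclosure falls on Monday, IVR day 3, and 7 − 3 = 4 of the 7 days come later.
- Passing the rule needs 4 days with a call. Failing it needs 4 days without one. Neither can be settled before IVR day 4, and make-up calls can postpone it further.

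If the call is made on schedule in an ordinary week, every decision under the rule therefore follows disclosure of AO versus therapy. Between 4 and 6 of the 7 baseline IVR days also come after the disclosure day.

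The CAPS and Form 90 are taken at the baseline appointment, before that call. The CAPS score is itself a balancing factor for randomisation, so it must also precede allocation.

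**2. Size (illustration; the inputs are assumptions, not protocol figures)**

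Let e be the proportion of an arm removed, and D the mean outcome of removed minus retained participants, in SD, taken as equal in all arms. In each arm

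mean(all) = mean(retained) + e × D,

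so the retained-only therapy-minus-AO difference is shifted by −D × (e_therapy − e_AO).

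Chance of failing 4 of 7, assuming independent days, a constant daily call probability p and no make-up calls, is P(X ≤ 3) for X ~ Binomial(7, p):

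| p | 0.9 | 0.8 | 0.7 | 0.6 | 0.5 |
|---|---|---|---|---|---|
| P(fail) | 0.3% | 3.3% | 12.6% | 29.0% | 50% |

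Absolute shift, by removal rates in the two arms:

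- 3.3% and 12.6%: 0.0927 × 0.25 = 0.023 SD; 0.0927 × 0.5 = 0.046 SD.
- 3.3% and 29.0%: 0.2565 × 0.25 = 0.064 SD; 0.2565 × 0.5 = 0.128 SD.
- Harsher assumptions, 20–30% in one arm, 5–10% in the other and D of 0.5–1.0 SD: from (0.20 − 0.10) × 0.5 = 0.05 SD to (0.30 − 0.05) × 1.0 = 0.25 SD.
- Equal removal rates and equal D: 0.

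The direction is open. If AO loses more participants and those lost do worse, the retained AO arm looks better and the therapy effect is understated. If therapy loses more such participants, the effect is overstated.

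**3. Enrolment counts**

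41 + 38 + 22 = 101, and AO is 22/101 = 21.8% against 20% planned. This is unremarkable (probability of 22 or more under 20% allocation is 0.36). It cannot show how many people the rule removed.

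**The case against.** Four points for the plan carry weight.

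- **Mitigation.** Staff chase missed calls and can collect the data by phone. Calls are paid at the same rate in every arm, and AO participants are promised therapy afterwards. Removals may be few. This lowers the risk but does not make it equal across arms.
- **Current status.** The overview of final modifications does not repeat the 4-of-7 rule. It may have lapsed, but nothing says so.
- **CPT versus RP.** If the therapy is concealed until session 1, first-week removal cannot depend on which therapy was assigned. This stands, subject to item 4.7, which read literally has all three allocations disclosed in week one.
- **Primary outcomes.** The CAPS and Form 90 baselines precede disclosure. This stands too.

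Three stronger readings are tempting but not supported.

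- A reader might infer that the trial is not analysed by intention to treat. The protocol names no analysis set, and a statistical analysis plan, not shown, could keep these participants in. It could not, however, supply outcomes that were never collected.
- A reader might take the 60% rule as a second exclusion that falls on the therapy arms alone. It does concern only those waiting for a first therapy appointment, but no loss of eligibility is attached to it, and the later overview words it as an expectation.
- A reader might infer that the primary outcomes are adjusted for the IVR week. The protocol says no such thing; it links the daily data to the sequence of symptom change.

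**Conclusion.** The point holds, limited to therapy versus AO and to the daily IVR data. As written, the 4-of-7 rule declares people ineligible after randomisation and after AO versus therapy is disclosed, and the protocol describes no follow-up for them. This is a fault in the conduct rules, not a detail left to the analysis plan.

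The bias cannot be measured from the document. The illustrations span 0 to about 0.25 SD in either direction. They rest on assumed removal rates and outcome gaps; make-up calls would push the figure towards the lower end. The conclusion on timing rests on the disclosure call being made when the protocol says.

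CPT versus RP is largely unaffected in the first week provided session-1 disclosure was kept, and the in-person baselines are unaffected.

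**What to change.** **For a future design.** Complete the 4-of-7 IVR week before randomising, or at least before any allocation, including AO versus therapy, is released. The cost is that the first appointment or check-in call is scheduled somewhat later. No extra participants are needed. Enrolment totals are already reported, so this cannot help the present cohort.

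**For participants already randomised:**

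1. Do not apply the rule as an exclusion. Keep and follow everyone in the assigned arm, and treat missed IVR days as missing data.
2. State whether the rule was still in force under the final modifications, and whether the 101 are counted before or after it was applied.
3. Report by arm any participants removed under it.
4. In AO comparisons of IVR outcomes, do not treat IVR days after disclosure as a pre-randomisation baseline. Use the in-person baseline measures as covariates.
5. Reconcile STUDY DESIGN item 4.7 with item 5.2, Safety and Comfort call and Therapy Visits on when CPT versus RP was disclosed.

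These steps need clarifying text and a count from existing study records. Outcomes never collected from people already removed cannot be recovered, and the report should say so.

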**Therapy Visits**

Participants randomized to a treatment condition meet with their therapist for 50 minutes twice per week for 6 weeks (rescheduled appointments may extend into the 12th week if necessary and the daily IVR calls will be extended to accommodate rescheduling). At each of 12 therapy visits participants provide breath alcohol concentrations (BACs). If their BAC is over a .02, the appointment has to be rescheduled.

Participants are informed of their study condition at the start of the first session. The therapy sessions themselves are provided by trained clinicians in a manualized fashion. As noted above, we attempt to conduct 12 therapy sessions in 6 weeks but can extend this period to as long as 12 weeks in order to accommodate participants’ schedules. Both therapies utilize in session and between session practice assignments. Once each week participants complete weekly self-report measures of PTSD and alcohol/drug use on paper for use by the study therapists to monitor symptom change and potential clinical issues. This weekly monitoring of symptom change is standard clinical protocol for CPT and RP. An assignment review is completed by participants at the start of sessions 2-12 to document the time spent on practice outside of therapy and level of usefulness to the participant.

**Assessment Only Check-ins and re-randomization**

During the 7-week daily monitoring period, the AO group receives weekly telephone calls from a study therapist to briefly check-in regarding safety and stability. Should marked clinical deterioration be noted either during a telephone check-in or via the daily IVR assessments, participants are carefully assessed regarding whether their continued involvement in the study is safe and the co-PI’s is consulted on this decision. At the end of their 7 weeks of IVR monitoring the AO participants are re-randomized to receive either CPT or RP but will not continue IVR monitoring during treatment. They are re-randomized using a separate randomization table that is balanced with respect to baseline severity of AUD, severity of PTSD symptoms and gender.

**Adverse Events and Serious Adverse Events**

All serious or unexpected adverse events are reported to the UW and VA IRBs as well as the NIAAA in accordance with requirements. We also inform our data safety monitors of serious adverse events and they review all adverse events annually. Please see information about ongoing safety monitoring above in the IVR monitoring section.

**Follow up Assessments**

When participants have completed 12 sessions of RP or CPT therapy, they come in for a post-test assessment and complete the following measures: 1) the CAPS, 2) Life Stressor Checklist, 3) Form 90, 4) PACS, 5) the PCL-C, 6) PHQ-9, 7) PMBS, 8) CSS, 9) Reasons for Drinking, 10) Additional PTSD Questions, 11) Other Mental Health Treatment, and 12) Contact Form. The clinical assessor is blind to treatment condition.

We again follow up with participants at 3-, 6-, 9- and 12- months after the completion of treatment. The 6- and 9- month follow ups include fewer measures (no CAPs, PMBS, or Coping Strategies Scale) and do not require an in person appointment. Instead, these two assessments are mailed to participants with a stamped, self-addressed envelope and will be accompanied by a short telephone call from the clinical assessor. The 12-month follow up assessment incorporates all the above measures and the Reactions to Research Questionnaire.

**Procedures for Protecting the Blind**

Because this study involves receipt of psychotherapy, it is only a single-blind study as there is no way to deliver the care without the participant knowing what they are receiving. To protect the single blind, we have taken measures to keep the study assessor blind to study condition including not having her attend portions of lab meetings that pertain to specific participants, keeping her tasks confined to any that do not have to do with enrolled participants other than conducting the assessments, and informing study participants repeatedly to not share what they have been doing in treatment with her.

**Study Discontinuation or Termination:**

**Premature discontinuation**

Participants are discontinued prematurely from study treatment if during the treatment phase additional interventions not prescribed by the protocol are required to manage marked deterioration of clinical status. Specifically, dangerousness toward self or others or emergence of acute symptoms necessitating hospitalization or additional psychotropic medications may be grounds for discontinuation from the study. If at any time during the study, substance use or psychiatric symptoms become markedly increased, resulting in severe patient distress or presenting immediate danger to self or others, the participant may be discontinued from the study. A retrieved dropout strategy is used to gather follow-up data at each of the subsequent assessment points if participants are willing to remain in the assessment portion of the study should that be determined safe and appropriate for them. Additionally, if participants evidence the need for medical detoxification services to safely manage withdrawal from alcohol they are assisted in locating inpatient detoxification services either at the VA (veterans) or in the community (non-veterans).

**Study termination**

Study completers finish their participation at the 12-month follow up assessment. Participants receive the study debriefing form and a copy of the community referrals at the final assessment appointment.

**SEQUENCE OF SYMPTOM CHANGE DURING AUD OR PTSD TREATMENT FOR CO-MORNID PTSD/AUD**

**Enrollment, Inclusion/Exclusion Criteria, Study Design, Questionnaires, & Compensations**

**Overview Reflecting Final Protocol Modifications**

**TARGET ENROLLMENT**

1. 5,000 phone screens.
2. 500 screening/baseline assessments.
3. 300 enrolled:
   1. 120 participants in the Cognitive Processing Therapy (CPT) group.
   2. 120 participants in the Relapse Prevention (RP) group
   3. 60 in the Assessment Only (AO) groups.

**TOTAL ENROLLMENT**

262 were consented and 101 were randomized

1. CPT: 41 participants.
2. RP: 38 participants.
3. AO: 22 participants.

**INCLUSION CRITERIA**

1. Men and women age ≥18 years.
2. A current DSM-V diagnosis of alcohol abuse/dependence.
3. Recent alcohol consumption criteria:
   1. Past Month Criteria:
      1. Recent alcohol consumption of > 14 (women) > or 21 (men) drinks per week for at least two weeks in the past 30 days OR
      2. At least two days of heavy drinking (≥ 4 drinks per day for women and ≥ 5 drinks per day for men) in the past 30 days.
   2. Past 90 Day Criteria:
      1. Any alcohol consumption in the past two weeks AND Either
      2. Recent alcohol consumption of >14 (women) or > 21 (men) drinks per week for at least two weeks in the past 90 days OR
      3. At least 2 days of heavy drinking (4 or more drinks per day for women and 5 or more drinks per day for men) in the past 90 days.
4. Desire to abstain from alcohol or reduce alcohol use.
5. Current DSM-V diagnosis of PTSD.
6. Capacity to provide informed consent.
7. English fluency.

**EXCLUSION CRITERIA**

1. Unstable psychiatric medication regimen (medication or dose changes in the past 30 days).
2. Current trauma-focused mental health treatment (MH) or behaviorally focused AD AD/MH treatment in the past 30 days.
3. Suicide attempts or serious self-harm in the past three months or suicidal ideation with intent or plan in the past two months.
4. Moderate to high risk for homicidality in the past six months.
5. Presence of an uncontrolled psychotic disorder or uncontrolled Bipolar Disorder in the past three months.
6. Delirium Tremens in the past six months.
7. Signs or symptoms of alcohol withdrawal at the time of initial consent.
8. Have taken Antabuse in the past 30 days or plan to take Antabuse in the next 30 days.
9. Unwilling or unable to provide one collateral contact.
10. Unwilling or unable to provide a valid SSN.
11. Unwilling or unable to commit to regular attendance at therapy appointments.
12. Participation in an experimental drug study or any type of addiction study in the past 30 days.
13. Unwilling to have assessments or therapy sessions recorded.
14. Current relationship involves severe domestic violence victimization within the past two months.
15. Awaiting sentencing or pending incarceration.
16. Currently in a PTSD or alcohol psychotherapy that involves regular written practice assignments.

**STUDY DESIGN**

1. Participants were recruited through:
   1. Advertisements placed at the HCSATS, ATC of the VAPSHCS Seattle Campus, community, such as libraries, laundromats, coffee shops, community and treatment centers, and other similar gathering places with public bulletin boards; community newspapers; and online.
   2. Provider referrals.
   3. Screening of the University of Washington (UW) Medical Center, UW Neighborhood Clinics, Harborview Medical Center, and Northwest Hospital medical records.
   4. Screening of the VA medical records quarterly, including records from the past 12 months.
   5. Invitation letter. The letter was mailed to subjects screened through medical records. It had information about the study aims, procedures, compensations, and voluntary nature of research participation. A business reply postcard was included in the mail to allow individuals to opt-out. When participants did not response within two weeks, the study staff made up to three follow-up calls to ascertain their interest in learning more about the study and possibly completing the phone screening.
2. Interested individuals called the UW or VA study coordinator and received an overview of the study. Repeated callers were ineligible for rescreening within 3 months.
3. Individuals who were interested in participating underwent a 15-20 minute screening phone interview to determine their eligibility:
   1. Eligible individuals were invited to schedule an in-person screening session at the VA or HCSATS. Individuals who were recruited through the VA were seen only at the VA for their screening and all of the other sessions.
   2. Ineligible individuals were offered community referrals by phone, mail, or email (email was allowed for UW participants only).
4. Screening Session:
   1. During this screening session, informed consent was obtained and, following consent, the individuals were asked to complete a consent quiz. The assessor reviewed the answers and explained the correct response to each missed question. If, after this discussion, the individuals did not seem able to comprehend the correct response to more than two items, the assessor used their clinical discretion to determine if the individuals were ineligible.
   2. Ineligible individuals were provided with a list of community resources.
   3. Eligible individuals took a breathalyzer test to ensure that they were sober during the session.
   4. Individuals whose Blood Alcohol Concentration (BAC) was over 0.0 were asked to either wait until their BAC drops to 0.0 or to reschedule the appointment.
   5. Individuals went through a 2.5- to 3.5-hour assessment to confirm eligibility and to complete questionnaires.
   6. Individuals who were found to be eligible were shown how to use the Interactive Voice Response (IVR) system and were introduced to the site study clinician who called them the next business day to check on symptom exacerbations, provide support and normalization or intervene clinically as needed, and provide IVR support:
      1. The AO participants called the IVR system daily for seven weeks before they were re-randomized.
      2. The CPT and RP participants called the IVR system for one to four weeks before they started their individual therapy (baseline monitoring period). When the baseline-monitoring period was extended due to conflicts in scheduling the first therapy appointment, the participants were expected to continue calling the IVR system at least 60% of the days.
   7. During the first week of IVR calls (baseline calls), the study staff called the participants to let them know if they were randomized into the CPT, RP, or AO group.
5. Treatment Sessions:
   1. Participants randomized to either the CPT or RP group met with their study clinician for 60 minutes twice per week for 6 weeks (rescheduled appointments could be extended into week 20.
   2. The therapist informed the participants of their study condition (CPT or RP) at their first therapy session.
   3. At the beginning of each treatment session, the participants:
      1. took a breathalyzer test. If their BAC was over 0.02, they were asked to wait until their BAC dropped below 0.02 or to reschedule.
      2. complete short questionnaires to track homework compliance.
   4. Participants were also asked to complete short weekly questionnaires to monitor their PTSD symptoms and substance abuse prior to the first therapy session of the week.
6. Assessments:
   1. Participants completed a post-treatment assessment within one month of completing their treatment.
   2. Participants repeated the assessment battery 3- and 12- months post-treatment.
   3. Participants were given a choice to complete the post-treatment, 3-month, and 12-month assessments in-person or by phone. The study assessor collected clinical measures already approved for use in the assessments in a short telephone interview.
   4. Participants were also asked to complete 6- and 9-month follow-up surveys via web. These surveys covered a similar range of topics as the other assessments (post-treatment, 3-month, and 12-month assessments), but were significantly shorter (the web surveys took approximately 45 minutes to complete). Participants were given a choice to complete a paper version of the survey if they do not have regular internet access or by phone.
   5. Participants had two months to complete each of the five follow-up assessments.
7. AO Participants:
   1. AO participants completed seven weeks of IVR monitoring following their screening session. To accommodate difficulties in scheduling the initial post-assessment and/or therapy session, the IVR calls could be extended into week 9th.
   2. Study staff called the AO participants weekly to monitor their safety and stability over the seven weeks of IVR monitoring. When there was marked clinical deterioration during either the telephone check-in or IVR assessments, participants received a clinical call from either a study clinician or one of the principal investigators and were carefully assessed regarding whether continued participation was safe.
   3. At the end of the seven weeks of IVR monitoring, the AO participants completed their first post-assessment. They were then re-randomized into CPT or RP.
   4. AO participants went through the same treatment sessions as the other participants, but did not complete IVR assessments during treatment.
   5. AO participants completed a second post-assessment at the end of their treatment and a 3-, 6-, 9-, and 12-month assessment. They had 2 months to complete each of the five follow-up assessments.
8. IVR Calls:
   1. Participants who partially completed or missed their IVR calls received a call from a study staff the next working day.
   2. Collection of IVR’s using paper and pencil were also offered to the participants.
9. Participants were debriefed and provided with a list of community resources at the final follow-up assessment or earlier if they left the study prematurely.
10. The follow-up time frame was reduced from 12 months to three months for participants who were enrolled after July 2017:
    1. CPT and RP participants attended:
       1. Screening session/baseline.
       2. Weekly therapy sessions.
       3. Post-therapy assessment.
       4. Three-month follow-up.
    2. AO participants attended:
       1. Screening session/baseline.
       2. Post-test follow-up #1.
       3. Weekly therapy sessions.
       4. Post-test follow-up #2 after completing the therapy session.

